### Randomization and blinding

Eligible patients are allocated at a 1:1 ratio to the experimental or control group, with competitive enrollment across centers. The randomization sequence is generated and assigned via the Interactive Web Response System (IWRS). A single-blind design is used.

### Intervention

Analgesics and sedatives administered prior to enrollment are discontinued. In the experimental group, patients receive intravenous nalbuphine hydrochloride (Yichang Humanwell Pharmaceutical Co., Ltd., China). A loading dose of 6 mg nalbuphine Hydrochloride is administered over 30 s (±10 s), followed immediately by initiation of a continuous maintenance infusion at a baseline rate of 2.0 mg/h. Five minutes after the loading dose, if the patient’s Critical-Care Pain Observation Tool (CPOT) score is greater than 2, a 2 mg supplemental bolus is given. This supplemental bolus may be repeated once, with a minimum interval of 5 min between doses, allowing up to two supplemental boluses within the first 20 min. The total dose, including the loading dose and any supplemental boluses, is capped at 10 mg, and no additional boluses are permitted beyond the initial 20-min period. Twenty minutes after the loading dose or once the cumulative dose reaches 10 mg, the maintenance infusion rate is titrated according to CPOT and Richmond Agitation-Sedation Scale (RASS) scores. Dose adjustments are made in increments of 0.5 mg/h, within a target range of 1.0–5.0 mg/h, with a minimum of 5 min between each adjustment. In the control group, patients receive hydromorphone hydrochloride (Yichang Humanwell Pharmaceutical Co., Ltd., China) via continuous intravenous infusion, initiating at 0.5 mg/h. The infusion rate is adjusted based on CPOT and RASS scores in increments of 0.5 mg/h within a target range of 0.5–3.0 mg/h, with at least 5 min between adjustments.

If a patient’s CPOT score remains above 2 despite reaching a nalbuphine infusion rate of 3.0 mg/h or a hydromorphone hydrochloride infusion rate of 2.0 mg/h, rescue sedation with propofol is initiated. Propofol is started at an initial infusion rate of 0.5 mg/kg/h and subsequently titrated in increments of approximately 25% of the current rate (0.125 mg/kg/h), within a dosage range of 0–4 mg/kg/h.

The study drug infusion is discontinued after 24 h (±10 min) of administration or earlier if the patient met weaning criteria and a spontaneous breathing trial is planned. Patients requiring ongoing analgesia or sedation after discontinuation of study drugs are managed at the investigator’s discretion.

### Electrolyte management

Given the well-established influence of electrolyte imbalances on pain perception, sedation efficacy and stability, and cardiovascular safety (Eisinger et al., 2022), serum concentrations of key electrolytes—including potassium, magnesium, calcium, and phosphate—will be measured at baseline and monitored daily throughout the study duration. Any clinically significant deviations from reference ranges will be promptly addressed in accordance with institutional clinical protocols. Patients exhibiting persistent, protocol-intractable electrolyte abnormalities—defined as those that remain uncorrected despite adherence to standard management guidelines and that may compromise the reliability of sedation assessments or elevate the risk of adverse cardiac or neurological events—will be systematically documented and included in the prespecified safety analyses.

### Outcomes

The primary outcome is the analgesic success rate during 24 h of study drug administration. Analgesic success is defined as the fulfillment of both criteria: 1) no administration of rescue analgesic medication, and 2) maintenance of a CPOT score ≤2 for at least 70% of the observation period during study drug infusion.

The secondary outcomes include: 1) The percentage of time within CPOT score ≤2 and RASS score between −2 and +1 during 24 h of study drug administration: This metric represents the proportion of time during which a patient maintains a CPOT score of ≤2 and a RASS score between −2 and +1, relative to the total duration of study drug administration. 2) The frequency and dosage of rescue sedation during 24 h of study drug administration: The frequency refers to the number of rescue sedative administrations, while the dosage indicates the total amount of propofol administered as rescue sedation during the infusion of the study drug. 3) The proportion of patients requiring rescue sedation during 24 h of study drug administration: This is the percentage of patients in each treatment group who received concomitant propofol for rescue sedation during study drug infusion, calculated as (Number of patients receiving propofol/Total number of patients in the group) × 100%. 4) The total cumulative dose of rescue sedative during 24 h of study drug administration: The sum of all propofol doses administered as rescue sedation during the period of study drug infusion. 5) The time to successful weaning and ICU discharge during 24 h of study drug administration: Time to successful weaning is defined as the interval from the initiation of the study drug to liberation from mechanical ventilation. Time to ICU discharge is defined as the interval from study drug initiation to actual ICU discharge. Successful weaning is achieved when the patient is extubated and subsequently maintains stable spontaneous breathing without the need for reintubation. 6) The weaning success rate and the proportion of patients discharged from the ICU: The weaning success rate reflects the percentage of patients successfully weaned from mechanical ventilation. The proportion of patients discharged from the ICU indicates the percentage of patients transferred out of the ICU within the observation period.

Safety outcomes include adverse drug reactions or adverse events occurring during the study. All patients are monitored throughout the trial period for any adverse events. The clinical manifestations, severity, time of onset, duration, interventions, and outcomes are recorded, and the potential relationship to the study drugs is assessed.

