## Methods

### Study design

This is a multicenter, randomized, single-blind, parallel, positive control study initiated by Yichang Humanwell Pharmaceutical Co., Ltd., China. Apart from our ICU, 15 ICUs from tertiary hospitals in China enroll patients in the trial. This study was registered at ClinicalTrials.gov (NCT06785571). The trial protocol is reported in accordance with the Standard Protocol Items: Recommendations for Interventional Trials (SPIRIT) guidelines (Calvert et al., 2018). Table 1 presents the scheduled process of enrollment, interventions, and measurements.

**TABLE 1 T1:** Scheduled process of enrollment, interventions, and measurements.

Timepoint	Study period				
	Enrollment	Allocation	Post-allocation		Close-out
	After admission to ICU	After obtaining informed consent	Before study drug administration	Study drug administration	12–48 h after study drug administration ended
Enrollment					
Eligibility screen	X	​	​	​	​
Informed consent	X	​	​	​	​
Allocation	​	X	​	​	​
Interventions					
Nalbuphine hydrochloride	​	​	​	X	​
Hydromorphone hydrochloride	​	​	​	X	​
Assessments					
Baseline variables	X	​	​	​	​
Vital signs	X	X	X	X	X
RASS score	X	X	X	X	​
CPOT score	X	X	X	X	​
Laboratory tests	X	​	​	​	X
APACHE II score and SOFA score					
Dose of drugs (study drugs, analgesics, vasopressors, rescue sedatives)	​	​	​	X	​
AEs and SAEs	​	​	​	X	​
Outcome variables	​	​	​	​	X

RASS, Richmond Agitation–Sedation Scale; AEs, adverse events; SAEs, serious adverse events.

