### Estimation of sample size

The sample size estimation is based on a non-inferiority design. According to previous findings and literature reports (Liu et al., 2018), nalbuphine is capable of maintaining the target analgesic effect within 3–24 h post-administration, with CPOT scores ≤2 for more than 70% of the time. An analgesic success rate approaching 100% is anticipated. We estimate an efficacy of 99% in the experimental group, and the control groups. Following consultation of several experts, the non-inferiority margin δ is set at −8%, meaning that an 8% reduction in efficacy representing the maximum clinically acceptable difference. A two-sided significance level of α = 0.05 and a power of 80% (β = 0.2) are applied. Sample size estimation is conducted using the Farrington and Manning method via PASS 2022 software, assuming a 1:1 allocation ratio between the two groups, and 73 participants per group is required. Assuming an anticipated dropout rate of approximately 12%, a total of 168 subjects is needed.

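### Analgesic success excludes rescue analgesia, but the only rescue described for persistent pain is propofol, labelled sedation and outside the primary endpoint; the two sections must be reconciled

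*Protocol article*

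**What the plan says.** **Outcomes section.** The definition opens: "Analgesic success is defined as the fulfillment of both criteria: 1) no administration of rescue analgesic medication". The two criteria together read: "1) no administration of rescue analgesic medication, and 2) maintenance of a CPOT score ≤2 for at least 70% of the observation period". Rescue analgesic medication is not defined there or elsewhere in the article.

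**Intervention section.** If the "CPOT score remains above 2 despite reaching a nalbuphine infusion rate of 3.0 mg/h or a hydromorphone hydrochloride infusion rate of 2.0 mg/h", then "rescue sedation with propofol is initiated". The trigger is a pain score, but the label is sedation. In the nalbuphine dosing text, "no additional boluses are permitted beyond the initial 20-min period".

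**Where propofol is scored.** It enters secondary outcomes 2 to 4, for example "The proportion of patients requiring rescue sedation during 24 h of study drug administration". Table 1 lists the recorded drugs as "Dose of drugs (study drugs, analgesics, vasopressors, rescue sedatives", with analgesics and rescue sedatives as separate items.

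**Estimation of sample size section.** The 99% success rate in both arms is supported by earlier findings "with CPOT scores ≤2 for more than 70% of the time". Rescue is not mentioned.

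**The concern.** The endpoint's rescue component and the protocol's rescue procedure use different terms. Read plainly, the step taken when the opioid has not controlled pain is not the event that criterion 1 counts. CPOT is a behavioural score, and the protocol answers a high score with a titrated sedative, so it expects propofol to lower the score. A patient in whom the opioid alone did not control pain could then be recorded as an analgesic success.

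In a non-inferiority comparison this matters in one direction. If the need for propofol is greater on nalbuphine, leaving it out moves both success rates towards 100% and the difference towards zero. The possibility is not remote: the Limitations section concedes that the chosen dose ratio of about 4:1 may underestimate the nalbuphine requirement. The primary result would then describe opioid with propofol available rather than the opioid itself.

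**Working it through.** **1. The plan's own figure.** Inputs from Estimation of sample size: 99% success in both arms, margin 8 points, two-sided α = 0.05 (one-sided 0.025), power 80%, Farrington-Manning, 1:1.

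n per arm = [(z₀.₉₇₅·s₀ + z₀.₈₀·s₁)/δ]²

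- Rates restricted to the null: 0.9149 and 0.9949, so s₀ = √(0.9149×0.0851 + 0.9949×0.0051) = 0.288.
- s₁ = √(2×0.99×0.01) = 0.1407.
- n = [(1.960×0.288 + 0.842×0.1407)/0.08]² = 72.9, so 73 per arm, as stated.
- With 12% dropout, 73/0.88 gives 83 per arm, 166 in total against 168 stated. The arithmetic is sound on its inputs and is not in dispute.

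**2. Does criterion 2 catch these patients anyway?** It tolerates CPOT >2 for 30% of the infusion: 0.30 × 24 h = 7.2 h, or 1.8 h of an assumed 6 h infusion. The earliest propofol start follows from the step rules in the Intervention section:

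- Nalbuphine: titration opens at 20 min, or once 10 mg has been given (as early as about 10 min). Two 0.5 mg/h steps lead from 2.0 to 3.0 mg/h, at least 5 min apart.
- Hydromorphone: three 0.5 mg/h steps lead from 0.5 to 2.0 mg/h, at least 5 min apart.
- In either arm propofol can start about 20 to 30 min after the start of study drug. That is 1.4% to 2.1% of 24 h, or 5.6% to 8.3% of 6 h, well inside the 30% allowance.

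So criterion 2 need not fail a patient whose score falls soon after propofol. It does fail one whose score stays high for more than 30% of the time.

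**3. How much can the definition matter?** The documents give no propofol-use rate, so the rates here are assumptions. Success if propofol is counted as failure = 0.99 × (1 − propofol use). If it is not counted and always works, success stays at 99%. The probability that the Miettinen-Nurminen lower 95% bound exceeds −8 points was obtained by exact enumeration of both binomials at 73 per arm.

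| Assumed propofol use (nalbuphine / hydromorphone) | Success if counted | True difference if counted | P(non-inferior), not counted | P(non-inferior), counted |
|---|---|---|---|---|
| 20% / 10% | 79.2% / 89.1% | −9.9 points | 86% | 1% |
| 30% / 15% | 69.3% / 84.2% | −14.9 points | 86% | 0.2% |
| 10% / 10% | 89.1% / 89.1% | 0 | 86% | 32% |
| 20% / 20% | 79.2% / 79.2% | 0 | 86% | 21% |

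In the first two rows the true difference lies beyond the margin once propofol counts, so a near-zero chance in the last column is built in. In the last two rows nothing is hidden; counting propofol only lowers power.

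**4. Consequence for the 99% assumption.** If propofol counts, success cannot exceed 1 minus propofol use. The same Farrington-Manning formula at equal true success gives:

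| Success in both arms | n per arm | Total with 12% dropout | Exact power at 73 per arm |
|---|---|---|---|
| 95% | 146 | 332 | 49% |
| 90% | 235 | 536 | 33% |
| 80% | 396 | 900 | 22% |

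**The case against.** **The term may be defined elsewhere.** This is a condensed article, and Table 1 records analgesics apart from rescue sedatives, so criterion 1 may be meant to catch non-study analgesics. Another reader could count pain-triggered propofol as rescue analgesia. This stands in part: the exclusion of propofol is inferred from separate terms and is nowhere stated. But the two published sections do not fit together, and the meaning of the primary endpoint depends on which reading is intended.

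**Criterion 2 still fails patients.** This stands. A reader might infer that the endpoint can fail patients only for a rescue drug that does not exist. The documents do not support that, because poor CPOT time is a failure in its own right.

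**The bolus restriction.** A reader might take it as a bar on all rescue analgesia. It sits in the nalbuphine dosing text and concerns study-drug boluses only.

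**Starting propofol is not the same as analgesic failure.** This stands. The triggers (3.0 and 2.0 mg/h) lie below the range maxima (5.0 and 3.0 mg/h) and are two titration steps from the starting rate in one arm and three in the other. Scoring every such start as failure would tie the endpoint to unequal triggers.

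**Masking would be visible.** Propofol use is compared between arms, secondary outcome 1 combines CPOT with RASS, and patients are woken for formal scoring before titration ends. This is true, but none of it enters the non-inferiority decision.

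**Conclusion.** The mismatch is real and should be resolved before the primary result is interpreted. Followed as written, a patient whose pain was controlled only after propofol can count as an analgesic success. If that need is greater on nalbuphine, the omission favours non-inferiority.

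The size is conditional. The contrast of 86% with 1% rests on assumed use of 20% versus 10%, on propofol always being effective, and on 73 evaluable patients per arm. It shows how far the conclusion can turn on an undefined term. A reader might take it as the trial's actual false-positive risk, but the documents contain nothing from which that could be estimated. Nor do they show that propofol use will differ between arms; with equal use there is no bias to find.

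A reader might also conclude that the primary definition must be replaced, or that non-inferiority should require both definitions to agree. Neither follows. With arm-specific triggers and power of roughly 20% to 30% under equal use of 10% to 20%, an agreement rule would amount to a co-primary requirement that the trial is not sized for.

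**What to change.** Reconcile the Intervention and Outcomes sections: state what rescue analgesic medication covers, and whether propofol started for CPOT >2 is a primary-endpoint failure.

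- **If it does not count:** pre-specify, as the first supportive analysis, the same Miettinen-Nurminen comparison with CPOT-triggered propofol scored as failure. Word the primary conclusion as non-inferiority with propofol rescue permitted.
- **If it does count:** restate the expected success rate and the power for that definition, since the article supports 99% only with the CPOT-time criterion.

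The cost of the first route is small: wording, plus one analysis on propofol data already recorded. Its limits should be stated with it. Power is low (at 84 per arm, half of the 168 planned and before dropout, about 24% if 20% in each arm need propofol), and the triggers differ by arm and lie below the range maxima. It should be read with those caveats and not as a second hurdle. The second route may need a much larger trial, as the last table in the working shows. Neither route changes a dose or a rescue rule, and none is proposed here.

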### Data collection and management

Upon enrollment, detailed patient demographic data (age, sex, body weight, ethnicity), medical history, clinical data (vital signs, ECG, laboratory tests), and comorbidities are collected. Vital sign monitoring includes heart rate, systolic and diastolic blood pressure (SBP/DBP), respiratory rate, and peripheral capillary oxygen saturation (SpO2). These parameters are recorded immediately at the initiation of the study drug administration (designated as T0), with subsequent assessments performed every 20 min during the first 2 h post-administration. From 2 to 24 h post-administration, or when weaning screening criteria are met and a weaning trial is planned, recordings are taken every 2 h. Additional recordings are obtained immediately following successful weaning and/or ICU discharge. Body temperature is recorded at T0 and again at 24 h post-administration or when weaning criteria are met. Continuous ECG monitoring is conducted throughout the study drug administration. Standard 12-lead ECG is obtained, and blood samples (for complete blood count, biochemistry, coagulation profile, and pregnancy test when applicable) are collected before randomization and within 12–48 h after discontinuation of the study drugs.

The CPOT and RASS scores are evaluated as baseline assessments prior to randomization. Routine evaluations are performed immediately after T0 and every 2 h thereafter. Prior to any dose adjustment, both scores are documented. After each adjustment, assessments are repeated every 5 min until clinical targets are met and no further dose modifications are needed. If the patient is in undisturbed sleep, the RASS score is recorded as unchanged from the previous value and annotated as “sleeping”. However, for final determination of titration cessation, patients are awakened for formal CPOT and RASS evaluation.

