### Statistical analysis

Statistical analyses will be performed using SAS software (version 9.4 or higher). Continuous variables will be presented as mean ± standard deviation for normally distributed data and median ± interquartile range for non-normally distributed data, whereas categorical variables will be summarized as frequencies and percentages. All statistical tests and confidence intervals (CI) will be two-sided, with statistical significance defined as a p-value less than 0.05. The difference in analgesic success rates between the experimental and control groups will be estimated using the Miettinen and Nurminen method to calculate the two-sided 95% CI. Non-inferiority will be established if the lower bound of this interval exceeds −8%. The proportion of time during which patients maintain a CPOT score ≤2 and a RASS score between −2 and +1 will be analyzed using the arcsine square root transformation, followed by between-group comparison via the t-test. Time from initiation of study drug to successful weaning and time to ICU discharge will be illustrated using Kaplan-Meier survival curves and compared using the log-rank test. The frequency and dosage of rescue propofol sedation, along with total propofol dose administered, will be compared between groups using either the t-test or Wilcoxon rank-sum test, depending on data distribution. The proportions of patients requiring concomitant propofol sedation, weaning success rate, and ICU discharge rate will be compared using the χ^2^ test or Fisher’s exact test. The incidence of adverse events will also be assessed using χ^2^ test or Fisher’s exact test.

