## Discussion

This protocol outlines a phase III, randomized, single-blind, parallel, positive-controlled clinical trial designed to evaluate the effectiveness and safety of nalbuphine hydrochloride for analgesia in mechanically ventilated ICU patients. The study is particularly meaningful as it reflects a growing emphasis on individualized and safer analgesia strategies in critical care. If nalbuphine hydrochloride demonstrates analgesic efficacy comparable to hydromorphone hydrochloride while offering a more favorable safety profile, it can provide clinicians with an important alternative to ICU analgesia. Such results could help reduce reliance on deep sedation and limit risks associated with prolonged exposure to full μ-agonist opioids. While the design of this study incorporates several notable strengths, it also has inherent limitations.

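### The primary success rule scores CPOT alone, so low scores reached under over-sedation, or only after propofol given for persistent pain, count as analgesic success, and the other outcomes show this only in part

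*Protocol article*

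**What the plan says.** All references are to the Protocol article.

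- **Outcomes, primary.** Success needs two things: no rescue analgesic, and "maintenance of a CPOT score ≤2 for at least 70% of the observation period during study drug infusion". Neither criterion uses RASS.
- **Outcomes, secondary 1.** RASS enters only here, as the share of infusion time in which "a patient maintains a CPOT score of ≤2 and a RASS score between −2 and +1". Statistical analysis treats it as a single percentage (arcsine square root, then t-test).
- **Intervention.** Both infusions are adjusted on CPOT and RASS. If CPOT stays above 2 at 3.0 mg/h nalbuphine or 2.0 mg/h hydromorphone, "rescue sedation with propofol is initiated". Propofol is labelled rescue sedation throughout and is counted in secondary outcomes 2 to 4. The infusion runs 24 h, or stops "earlier if the patient met weaning criteria and a spontaneous breathing trial is planned".
- **Data collection and management.** "Routine evaluations are performed immediately after T0 and every 2 h thereafter". Scores are also taken before each dose change and at 5-minute intervals after it until targets are reached. In undisturbed sleep "the RASS score is recorded as unchanged from the previous value", with an annotation.
- **Statistical analysis.** "Non-inferiority will be established if the lower bound of this interval exceeds −8" percent, using a two-sided 95% Miettinen-Nurminen interval.
- **Discussion.** If efficacy is comparable and safety better, "Such results could help reduce reliance on deep sedation".

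**The concern.** CPOT is a behavioural score. The protocol itself answers a persistently high CPOT with a sedative, so it expects sedation to help bring the score down. The primary rule then credits the lower score as analgesia, whatever the sedation depth and whether or not propofol was needed.

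This matters for the comparison only if the arms differ. They could. Counting 0.5 mg/h steps from the starting rate, nalbuphine reaches its propofol threshold in (3.0 − 2.0)/0.5 = 2 steps and hydromorphone in (2.0 − 0.5)/0.5 = 3. Only nalbuphine has a loading dose and boluses. The Limitations section concedes that the doses are not precisely equipotent. If one arm is sedated more deeply, or gets propofol more often, its success rate includes time that is not clearly due to the study analgesic, and the non-inferiority verdict shifts in that arm's favour. If the arms are alike, there is no such bias.

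The Discussion also looks ahead to less reliance on deep sedation, yet no named outcome measures deep sedation by itself.

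**Working it through.** **1. The plan's own figure.** Inputs from Estimation of sample size: 99% success in both arms, margin −8%, two-sided α 0.05, power 80%, Farrington-Manning. The restricted estimates at a difference of −0.08 are 0.9149 and 0.9949.

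- s0 = √(0.9149 × 0.0851 + 0.9949 × 0.0051) = 0.2880
- s1 = √(2 × 0.99 × 0.01) = 0.1407
- n = [(1.960 × 0.2880 + 0.842 × 0.1407)/0.08]² ≈ 72.9, so 73 per arm, as stated.
- With 12% dropout, 73/0.88 rounds up to 83 per arm, or 166 in total, against the stated 168 (84 per arm).

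The sizing is sound, so the point does not rest on it. The expected failures per arm are only 0.01 × 73 = 0.73 to 0.01 × 84 = 0.84.

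**2. The rule applied to two patients, 24 h infusion, no rescue analgesic.**

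- *Patient A:* CPOT ≤2 and RASS −3 throughout. Controlled time is 24/24 = 100%, at least 70%, so a success. Secondary 1 is 0%.
- *Patient B:* CPOT above 2 at the propofol threshold rate; propofol is started and CPOT then stays ≤2. Success needs 0.70 × 24 = 16.8 h, so up to 24 − 16.8 = 7.2 h above 2 is tolerated. B is a success if CPOT came down within that allowance.

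**3. How much over-sedated time changes a patient's status.** Assume CPOT ≤2 throughout and no credit for time at RASS ≤ −3. Uncredited time must exceed 30% of the infusion: 7.2 h of 24 h, 3.6 h of 12 h, or 1.8 h of 6 h (early stopping is allowed). If every score were a 2-hourly reading standing for 2 h, that would be 4 of 12, 2 of 6 or 1 of 3 readings. That conversion fails once a dose change triggers 5-minute scoring, so the hours are the figures to use.

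**4. What secondary 1 can show.** A value of 60% can mean 40% of the time in pain, 40% agitated or 40% over-sedated. Low secondary 1 with high primary success points to RASS out of range, but does not say in which direction.

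**5. Sensitivity of the verdict to a few patients.** Miettinen-Nurminen two-sided 95% lower bound (restricted maximum likelihood, factor N/(N − 1)); non-inferior if above −8%.

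| Failures, nalbuphine vs hydromorphone | 73 per arm | 84 per arm |
|---|---|---|
| 0 vs 0 | −5.03% | −4.40% |
| 1 vs 0 | −7.39% | −6.46% |
| 2 vs 0 | −9.48%, not shown | −8.30%, not shown |
| 1 vs 1 | −6.16% | −5.39% |
| 2 vs 1 | −8.28%, not shown | −7.25% |
| 3 vs 3 | −7.87% | −6.90% |

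At 84 per arm, 3 vs 1 gives −8.97% (not shown) and 3 vs 2 gives −7.93% (non-inferior). A net shift of one or two patients can decide the verdict, depending on the starting counts.

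**6. Chance of showing non-inferiority.** Exact binomial enumeration of the same test. The failure rates are assumptions; the documents give none for a sedation-aware rule.

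| Failure rate, nalbuphine / hydromorphone | 73 per arm | 84 per arm |
|---|---|---|
| 1% / 1% | 86% | 89% |
| 2% / 1% | 62% | 68% |
| 3% / 1% | 40% | 47% |
| 1% / 3% | 93% | 97% |
| 2% / 2% | 70% | 80% |

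The direction decides whether the current rule helps or hurts nalbuphine. The last row is loss of power, not bias.

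**The case against.** The other side has five serious arguments.

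- **An analgesia endpoint may be scored on a pain scale, and supportive analyses belong in the SAP.** An absent sensitivity table would indeed be no finding in a condensed article. But the primary definition is stated here, and what it credits follows from its own wording.
- **Much is already handled.** Both infusions are titrated on RASS, patients are woken before titration is declared finished, a need for deep sedation is an exclusion, secondary 1 combines CPOT with RASS, three outcomes count propofol, and over-sedation could be reported as an adverse event. This stands as mitigation and limits how often the problem can arise. None of it enters the success rule or isolates over-sedation. The sensitivity analyses named under Limitations (potency assumptions, illness severity, sedative use, delirium) do not address sedation depth.
- **Long over-sedation is unlikely under titration.** More than 7.2 h at RASS ≤ −3 would need titration to be ignored or sedation to persist at the lowest dose. This also stands, and is one reason why the frequency is left open.
- **Nothing in the documents says CPOT is invalid at RASS −3.** Correct. A reader might infer that such patients are false successes, which the text does not support. It supports only that the rule cannot tell analgesia from sedation in that time.
- **The range −2 to +1 is not called a target in the Intervention section, and deep sedation in the exclusion criteria means RASS −4 or −5.** Both are right. The range is the only acceptable RASS range the article gives, and RASS ≤ −3 is over-sedation relative to it, not deep sedation as the protocol uses the term. The two need separate reporting.

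**Conclusion.** The point holds as a gap in a stated rule. CPOT ≤2 under over-sedation, or reached only after propofol for persistent CPOT above 2, is credited as analgesic success, and the listed outcomes expose this only in part.

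The size cannot be computed, because the documents give no RASS distribution and no propofol rates. The tables above show how fragile a 99%-success design is to any reclassification; they do not measure this one. A reader might infer that the trial is biased towards nalbuphine, or that its verdict is unsafe. The documents support neither: direction and frequency are unknown, and balanced reclassification up to 3 vs 3 failures leaves the verdict as it was. The propofol part rests on reading rescue analgesic as excluding propofol, which the article consistently calls rescue sedation.

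It is worth settling before unblinded data are seen, but it does not require redesign.

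**What to change.** Keep the primary outcome, secondary 1, the margin and the sample size. Prespecify:

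1. **Supportive analysis of the primary, sedation depth.** Time at RASS ≤ −3 stays in the denominator but is not credited as controlled. Use all recorded assessments, including the 5-minute ones after a dose change. Show readings annotated as sleep both carried forward and excluded. Carrying forward alone does not remove the problem: a carried −3 counts sleep as over-sedation, and a carried −1 can hide it. Use the same Miettinen-Nurminen interval and −8% margin.
2. **Supportive analysis of the primary, propofol.** Separately, count propofol started for persistent CPOT above 2 as failure, with the same interval and margin.
3. **Descriptive outcome by arm.** Report the share of infusion time and the proportion of patients with RASS ≤ −3, and the same for RASS −4 or −5 (deep sedation in the exclusion criteria), each with a difference and 95% CI.

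The cost is a few lines of text and a few tables from RASS, CPOT and propofol records already collected, with no new assessments or patients. For item 2, the reason for starting propofol must be identifiable from the CPOT and infusion-rate records. The downside is a few extra comparisons, to be labelled supportive or descriptive.
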